# Effectiveness of a novel mobile health education intervention (Peek) on spectacle wear among children in India: study protocol for a randomized controlled trial

**DOI:** 10.1186/s13063-017-1888-5

**Published:** 2017-04-08

**Keywords:** Uncorrected refractive errors, Children, School eye health, India, Spectacle wearing rate, Health education, Portable eye examination kit, Peek, Randomized clinical trial

## Abstract

**Background:**

Uncorrected refractive errors are the commonest cause of visual loss in children despite spectacle correction being highly cost-effective. Many affected children do not benefit from correction as a high proportion do not wear their spectacles. Reasons for non-wear include parental attitudes, overprescribing and children being teased/bullied. Most school programmes do not provide health education for affected children, their peers, teachers or parents.

The Portable Eye Examination Kit (Peek) will be used in this study. Peek has applications for measuring visual acuity with software for data entry and sending automated messages to inform providers and parents. Peek also has an application which simulates the visual blur of uncorrected refractive error (SightSim).

The hypothesis is that higher proportion of children with uncorrected refractive errors in schools allocated to the Peek educational package will wear their spectacles 3–4 months after they are dispensed, and a higher proportion of children identified with other eye conditions will access services, compared with schools receiving standard school screening.

**Methods/Design:**

Cluster randomized, double-masked trial of children with and without uncorrected refractive errors or other eye conditions. Government schools in Hyderabad, India will be allocated to intervention (Peek) or comparator (standard programme) arms before vision screening. In the intervention arm Peek will be used for vision screening, SightSim images will be used in classroom teaching and will be taken home by children, and voice messages will be sent to parents of children requiring spectacles or referral.

In both arms the same criteria for recruitment, prescribing and dispensing spectacles will be used. After 3–4 months children dispensed spectacles will be followed up to assess spectacle wear, and uptake of referrals will be ascertained.

The cost of developing and delivering the Peek package will be assessed. The cost per child wearing their spectacles or accessing services will be compared.

**Discussion:**

Educating parents, teachers and children about refractive errors and the importance of wearing spectacles has the potential to increase spectacle wear amongst children. Innovative, potentially scalable mobile technology (Peek) will be used to screen, provide health education, track spectacle wear and adherence to follow-up amongst children referred.

**Trial registration:**

Controlled-Trials.com, ISRCTN78134921. Registered on 29 June 2016.

**Electronic supplementary material:**

The online version of this article (doi:10.1186/s13063-017-1888-5) contains supplementary material, which is available to authorized users.

## Background

Uncorrected refractive errors (uRE) are the commonest cause of visual loss in children.

The proportion of visual impairment due to uREs, defined as ≤6/12 in the better eye, in a group of standardized studies of children aged 5 to 15 years was 56.0% in Nepal [1], 56.3% in Chile [2], 61.0% in rural India [3], 63.6% in South Africa [4], 81.7% in urban India [5], 87.0% in Malaysia [6], 89.5% in rural China [7] and 94.9% in urban China [8]. Correcting refractive errors (RE) is highly cost-effective [9–11]. It is estimated that 12.8 million children worldwide are visually impaired from uRE [12].

Refractive errors can result from the axial length of the eye being too long or too short, and from abnormalities in the curvature of the cornea. The three most common types of REs are myopia (short-sightedness), hypermetropia (long-sightedness) and astigmatism (distorted vision at distance and near). Myopia is the commonest type of RE [13]. The onset is usually around the age of 8 years and increases in severity throughout adolescence [13]. Myopia is far more common in Southeast Asian children, where the age of onset is earlier and progression more rapid [13]. There is increasing evidence of the impact of correcting RE in children, with improvement in social development, quality of life, visual functioning and academic performance [14].

In India, there are approximately 140 million children aged 11–15 years, 5.6 million (4%) of whom have uRE and would benefit from spectacles. Correction of REs is a priority of the Government of India [15]. However, a high proportion of children who could benefit from RE correction do not wear their spectacles [16], reported as only 30% in a recent study in India [17]. There are many reasons for non-wear, including parents not purchasing spectacles, overprescribing and children being teased and bullied or not liking their spectacles [16]. Some parents fear that spectacles will weaken their child’s eyes, are expensive and are stigmatizing, or indicate that their child has a disability [18]. In India, some programmes have trained teachers to screen vision, but teachers are not usually otherwise engaged in the process and they usually do not promote or monitor spectacle wear. It is not standard practice in India to send explanatory pamphlets to parents of children requiring spectacles and parents are not typically made aware of the benefits of spectacle wear.

There have been three trials of interventions to improve spectacle wear: an education intervention of students in China, which had negative results, showing that educating children alone is not effective [19]. Another recent trial in China had a factorial design with six subgroups. Children in half the schools were randomized to a health education intervention, which involved showing children a 10-minute documentary-style video, a booklet of cartoons, and classroom discussion led by teachers. The same schools were randomized to three approaches to providing spectacles i.e. free spectacles, a voucher, or children were given a prescription for spectacles. Spectacle wear was assessed by observation and self-report. Observed wear was higher in all four subgroups randomized to the health education intervention (RR 1.46 to 1.74) [14]. The other trial was of free versus low-cost spectacles in Tanzania, in which free spectacles almost doubled wearing rates [18].

A recent trial by the investigators in Bangalore, India showed that 2.6% of children aged 11–15 years had significant uRE, defined as a level of visual loss due to RE which improved by two or more lines of Snellen visual acuity (VA) in one or both eyes with spectacle correction. In this study, children could select the spectacle frames they preferred and almost 75% were wearing their spectacles at unannounced visits 3–4 months later [20].

Mobile phone technology is a rapidly expanding area in health care [21], including eye care [22]. A recent development, the Portable Eye Examination Kit (Peek) [23] has a suite of applications (apps), including for measuring VA [24] which has been found to be an acceptable tool for patients, examiners and stakeholders in a recent study in Kenya [25]. The Peek School Screening system enables automated text and voice messaging to parents/guardians and contact teachers as well as real-time notifications to refractive or hospital services of screened positive children who require further assessment or follow-up. Peek also has an app which generates images that simulate the visual blur associated with uRE (SightSim). (See Additional file 1: Figure S1.) A recent trial in schools in Kenya using the system demonstrated that teachers could be taught to screen VA reliably using the Peek app, and SightSim images (Polaroid photographs) and text messages were sent to parents. Uptake of referrals to eye care providers was two and a half times higher in the Peek intervention arm of the trial (unpublished data).

Research on why children with significant refractive errors do not wear their spectacles is limited, but the available evidence highlights the importance of environmental factors, particularly the negative attitudes of others i.e., peers, parents, the wider family and teachers, as well as community norms and attitudes [26, 27]. There are multiple theories and constructs which can be used to describe behavior or to bring about behavior change, and the Social Ecological Model (SEM), which describes five nested, hierarchical levels which influence behavior i.e., individual, interpersonal, organizational, community and public policy, has been adopted in this study as it encapsulates the main factors which influence spectacle wear among children [28]. The SEM emphasizes that it is easier to adopt healthier behaviors by bringing about change in the environment, by using the example of role models, and by reinforcement. In the trial being planned, SightSim images of relevance to Indian children aged 11–15 years will be used, including images of role models such as sports personalities, and used in classroom teaching so that all children as well as teachers learn about the impact of uRE and the impact of correction. Children identified who need spectacles will also take home a SightSim image of their choice to show their parents, which demonstrates how much clearer their child’s world would be if they wore their spectacles. Messages will be reinforced to parents through voice messages send to their mobile phones.

### Purpose

The purpose of this cluster randomized trial is to evaluate whether a health education package for teachers, parents and children (aged 11–15 years), delivered using Peek increases spectacle wear at 3 to 4 months and uptake of referral of children identified with other eye conditions.

The trial will also assess the cost of developing and delivering the Peek health education intervention and the cost of dispensing and delivering the spectacles in both arms of the trial. The cost per child wearing their spectacles at follow-up will be compared between the two arms of the trial.

The hypothesis is that the proportion of children wearing spectacles 3–4 months after they were given their spectacles is higher in schools allocated to the innovative Peek educational package than in schools randomized to the standard programme. The uptake of referrals is also anticipated to be higher in the schools allocated to the Peek educational package than those randomized to the standard programme.

### Formative research and pilot study November 2016

Formative research including a pilot study will be undertaken in non-trial schools to test all aspects of the trial, including which SightSim images to use and the content of voice messages to parents to remind them to encourage their children to wear their spectacles, or to access services. The formative research will use mixed methods, including focus group discussions separately with head teachers, parents of both boys and girls of different ages and also boys and girls of different ages. Focus group discussions with head teachers will gather their views of spectacle wear by children, views on using SightSim images to increase awareness among parents, and which images they consider the most suitable for parents.

Based on data from the focus group discussions, images will be selected for classroom teaching. These classroom education materials will be shown to children and they will be asked to give their opinion on activities that children with uncorrected refractive error might like to do but cannot do because they do not have clear enough vision. Children will be shown SightSim images of the visual blur experienced by children with uRE and they will be asked to express their reactions. Classroom teachers will also be asked to comment on the images suggested.

A short questionnaire to assess children’s knowledge of and attitudes towards spectacle wear will be assessed immediately before and after a session of classroom teaching using SightSim images. In each school, two classes of different ages will be administered the questions before and after classroom teaching, a total of approximately 200 children aged 11–15 years.

## Methods/design

The trial is designed as a cluster randomized, double-masked clinical trial of children with and without uRE in accordance with the Standard Protocol Items: Recommendations for Interventional Trials (SPIRIT) guidelines [29]. Children will be masked to the allocation as they will not be told that other schools will have a different intervention, and field workers who collect the data for the primary outcome will also be masked to the hypothesis and intervention arm.

### Study setting

The trial is being undertaken in government middle and secondary schools in urban and rural areas in and around Hyderabad, Telangana State, India. The trial is being coordinated by the Public Health Foundation of India (PHFI), Hyderabad. The team consists of a programme manager, administrator, optometrists, dispensing opticians, field workers and ophthalmologists. Training, quality assurance and oversight of data collection are being provided by staff at the International Centre for Eye Health, London School of Hygiene & Tropical Medicine (LSHTM).

### Participant eligibility

#### Selection of schools

A list of government secondary schools will be obtained from the District Block Education Officer. The precise location of each school will be determined using Google Maps. Schools will be excluded if they already have school eye health programmes where screening took place within the previous 2 years, or are single-gender schools. If two schools are less than 10 km apart one will be excluded at random. Schools will be stratified by location (urban/rural) and size (more or less than 200 children aged 11–15 years).

The head teacher of each selected school will be visited by a field worker to obtain written informed consent for the school to participate. An information sheet in the local language with an opt-out option will be given to each child aged 11–15 years for them to take home. Parents will be given the option to opt out entirely i.e., that their child is not screened, or to opt out from being recruited to the trial.

#### Inclusion criteria

There are two mutually exclusive eligibility criteria in this study i.e. for spectacle correction and for referral. Common criteria for both are that children are aged 11–15 years inclusive, parents’ consent for their child to take part in the study and the child proves assent, and they have a presenting VA (i.e. with spectacles if usually worn) of less than 6/9.5 in one or both eyes. Children will be eligible for immediate spectacle correction if their binocular VA with full correction improves by two or more lines. Children will be eligible for referral if they require cycloplegic refraction, if their presenting VA is 6/60 or less in one or both eyes regardless of the cause, if their best-corrected visual acuity does not improve by two or more lines in both eyes or they require further investigation for any other non-refractive eye conditions.

#### Exclusion criteria

Children will not be recruited if parents do not consent or the child does not assent. Children whose parents agree that they can be screened will be assessed and spectacles dispensed if required, or they will be referred, but will not be recruited to the trial. Children whose parents opt out entirely, but where the teacher suspects a problem will be given a letter to take home.

### Eligibility of those performing interventions

All refractions, prescribing and dispensing are being undertaken by fully qualified optometrists, with training and quality checks by the lead investigator. All screening, delivery of spectacles and follow-up at 3–4 months will be conducted by trained field workers.

### Identification of potential participants and recruitment

In the intervention arm, field investigators in the school identified by the head teacher will first undertake classroom teaching using the SightSim images for all children aged 11–15 years, after training. A training manual will be developed to standardize the delivery. Field workers will be trained in each school to screen VA using the Peek vision screener app at the Snellen equivalent 6/9.5 level of VA, and children aged 11–15 years will be screened. To pass vision screening a child needs to correctly see four or five of five consecutive E optotypes. Once screening has been completed, all those who fail will be automatically referred to a visiting optometrist and will be refracted on the same day. Attendance will be checked against the data in the Peek software. After identifying children requiring spectacles each child will select a SightSim image of their choice from a range of images, which they will be asked to take it home to show their parents.

In the schools allocated to the comparator arm, trained field workers will screen VA using a standard card-based E optotype at the 6/9.5 level at 6 meters. To pass at the 6/9.5 level children need to correctly indicate the orientation of the E in at least four out of five optotypes. No health education materials or voice messages will be sent to the parents (Fig. 1).

**Fig. 1 Fig1:**
[figure not shown]
Study flowchart

To standardize data recording, data will be entered using dedicated Peek software in both arms of the trial. The software will have range and consistency checks built in. Field workers and optometrists working in schools in both arms of the trial will be given tablets for data entry, and data will be regularly backed up onto a cloud server. In both arms of the trial the head teacher will be given a list of all the children in their school who require spectacles or referral. Classroom teachers will also be given a list of children in their class who require spectacles or referral.

The following information will be collected by trained field workers by interviewing all eligible children in both arms of the trial: name, age, gender, class and date of birth; parents’ mobile phone number, language used in the home; parental education; occupation of parents; whether one or both parents wear spectacles for distance vision and limited information on household assets taken from National Household Survey questionnaires. Data on subjective refraction and best-corrected VA in each eye will be recorded as well as the prescription of the spectacles required and the frame the child selected from a selection of thirteen plastic frames of different colours. In the intervention arm, the SightSim image the child selects to take home will be recorded.

In both groups of schools, only children with significant REs will be prescribed spectacles i.e., where after correction, the acuity improves by two or more lines binocularly. Children will select the frames they prefer from a range of coloured plastic frames. Each pair of spectacles will have a unique code. Spectacles will be delivered to the schools by field workers at no cost as soon as possible and all children in each school will receive their spectacles on the same day. At the school, field workers will double-check the name of each child against the lists given to classroom teachers, to ensure that each child receives the correct spectacles. The field workers will measure children’s VA with their new spectacles.

In both arms of the trial, children with other eye conditions will be referred using a referral slip indicating their study ID, name and school, indicating that assessment and treatment will be provided at no cost at Pushpagiri Eye Institute on presentation of the referral slip. An administrator will be appointed at Pushpagiri Eye Institute who will access lists generated by Peek software of all children referred. The administrator will enter the date of attendance of children who attend Pushpagiri Eye Institute into Peek software for children referred from the intervention and comparator arms of the trial.

In the intervention arm of the trial, voice messages will be sent to parents of children requiring spectacles in the local languages within 1 week of their child being given their spectacles and again every 2 weeks for 3 months. Reminder messages will also be sent to parents of children referred within 1 week of referral and again every 2 weeks for 3 months if their child has not attended.

Fieldwork has been planned such that the initial assessment, delivery of spectacles and follow-up 3–4 months later do not coincide with school examination periods, long school holidays, nor the end of the school year when children may leave or change schools.

If the Peek education package is found to be superior to the control schools, the same package will be delivered after the 3–4 month follow-up.

### Participant timeline and study flowchart

The study flowchart and participant timeline are presented in Figs. 1 and 2, respectively. A filled Standard Protocol Items: Recommendations for Interventional Trials (SPIRIT) checklist is available (see Additional file 2).

**Fig. 2 Fig2:**
[figure not shown]
SPIRIT timeline

### Intervention and comparator arm

The intervention will be the Peek Acuity health education package. The comparator will be a standard school screening programme where no health education materials or messages are sent to parents (standard care) (Table 1).

**Table 1 Tab1:** An overview of the two arms of the trial

	Intervention arm	Comparator arm
Age group	11–15 years	11–15 years
Screening VA level	<6/9.5 in one or both eyes	<6/9.5 in one or both eyes
Method of screening	Peek E Acuity by field workers	E card optotype by field workers
Health education	• SightSim images for classroom teaching by field workers, after orientation i.e. for all children	None
	• Eligible children will select a SightSim image of their choice from a range of pre-tested images to take home to show their parents with wording in the relevant local language	
	• Personalized voice messages for parents in the relevant local language	
Refraction	Trained optometrist	Trained optometrist
Definition of significant RE	Same in both arms of the trial	Same in both arms of the trial
Dispensing criteria	Same in both arms of the trial	Same in both arms of the trial
Frame types	Same in both arms of the trial	Same in both arms of the trial
Delivery of spectacles	Same in both arms of the trial	Same in both arms of the trial
Assessment of primary outcome	Same in both arms of the trial	Same in both arms of the trial

*VA* visual acuity, *Peek* Portable Eye Examination Kit, *RE* refractive errors

### Sample size calculation

A superiority margin of 20% was chosen to balance the anticipated higher costs of developing and delivering the Peek package. We estimate that we will need a study size of 450 children (225 in each arm) to detect a difference of 20% in spectacle wear between the intervention and comparator arm, assuming approximately 60% of children in the control arm will be wearing spectacles at follow-up, with a 95% confidence interval and 90% power. We have adjusted the sample size calculations for clustering using data from our previous study (unpublished) to estimate a design effect of 1.5. We have increased the sample size by 20% to allow for loss to follow-up. A total of 17,300 children will need to be screened to recruit 450 children for this trial. The communities are stable and few study children are expected to leave the school during the school year.

This will detect a 20% difference in spectacle wearing, determined using the sampsi command in Stata Statistical Software version 14 (StataCorp, College Station, TX, USA).

### Randomization

A list of schools where the head teachers has given permission will be prepared in India (PM) and each school will be allocated a unique ID. All clusters will be randomized at once so allocation concealment will not be an issue. The schools will be randomized using a web-based randomization service (Sealed Envelope Ltd. 2016. Simple randomisation service [Online]). Available from: https://www.sealedenvelope.com/simple-randomiser/v1/ [Accessed 3 Jan 2017])

The schools will be randomly allocated to intervention or comparator arm, stratified by size, i.e. the number of children enrolled at the school between the age 11–15 years. To reduce contamination, schools will be allocated to the intervention and control arm and not individual children, and study schools will not be closer than 10 km to minimize contact between children in the different arms of the trial. Recruitment bias will be unlikely because all children who fail screening i.e. who have a VA of less than 6/9.5, will have similar procedures thereafter, i.e. refraction, dispensing spectacles or referral, apart from the health education intervention, which will be applied after recruitment. Figure 1 is a flowchart showing a child’s journey and the activities involved from screening, to deciding whether they are eligible for recruitment, then randomization and follow-up.

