#### Primary outcome

The proportion of children wearing or having their spectacles with them at school at 3 to 4 months will be compared between the intervention and standard arms using the risk difference with 95% confidence intervals adjusted for cluster (school).

A separate analysis will also be undertaken to adjust for factors that may affect spectacle wear such as gender, age (linear term), degree of refractive error in the better seeing eye (linear term), previously wore spectacles (binary data), parental spectacle wear (binary data) and educational level (categorical data) if there are imbalances between the two arms of the trial. There will be no subgroup analysis.

In the Peek software the name of the school will never be entered, only the school study ID and the allocation code. The same applies to schools in the comparator arm. Schools will, therefore, only be identified by ID number while the data are being analysed.

Masked analysis of the primary outcome will be difficult as the database for schools allocated to the intervention arm will a larger number of fields than the comparator arm e.g., the SightSim image the child took home; the number and date of voice messages sent to parents.

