#### Secondary outcomes

The proportion of children who access eye care after referral to Pushpagiri Eye Institute will be compared between arms, using the risk difference with 95% confidence intervals adjusted for cluster (school).

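### The allocation strata are stated in two ways (location and size, or size only) and the planned cluster-only intervals include neither, which costs some precision but does not inflate false positives

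*Protocol article*

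**What the plan says.** Two sections of the protocol article describe the stratification. Under Selection of schools: "Schools will be stratified by location (urban/rural) and size (more or less than 200 children aged 11–15 years". That makes two factors and four strata. Under Randomization: "The schools will be randomly allocated to intervention or comparator arm, stratified by size, i.e. the number of children enrolled". That is one factor; location is absent and the cut-point of 200 is not repeated. The same section adds that "The schools will be randomized using a web-based randomization service", without describing how strata are applied.

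Under Data analyses, the primary outcome is compared "using the risk difference with 95% confidence intervals adjusted for cluster (school". The secondary outcome, referral uptake, "will be compared between arms, using the risk difference with 95% confidence intervals adjusted for cluster (school". A separate analysis of the primary outcome is to "adjust for factors that may affect spectacle wear such as gender, age (linear term), degree of refractive error in the better seeing eye", followed by previous spectacle wear, parental spectacle wear and educational level. It is done only "if there are imbalances between the two arms of the trial". Neither school size nor location is named in any of these analyses.

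**The concern.** The stratification factors are a core design feature, and a reader cannot tell from the article whether schools were allocated within two strata or four. The dissemination section commits to CONSORT reporting for cluster trials, so the factors actually used will have to be stated.

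The second part concerns the match between design and analysis. Stratified allocation balances the arms on the strata, so differences between strata no longer contribute to the sampling error of the risk difference. An interval that ignores the strata still counts those differences as noise. Location could plausibly matter here: the schools are urban and rural, and every referral goes to one institute. At stake are the width of the two main intervals and some power. The estimated difference also decides whether the cost analysis is done, since that requires a difference of 20% or greater.

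**Working it through.** **1. The planned sample size.** Inputs from the Sample size calculation section: 60% against 80%, 95% confidence (read as two-sided 5%), 90% power, design effect 1.5, 20% loss. The continuity-corrected two-proportion formula gives 119 per arm. Then 119 × 1.5 = 178.5, and 178.5 / 0.8 = 223.1, rounded up to 224, against 225 stated. The figure reproduces and contains no term for strata, so the point below concerns the interval and not N. After loss, the effective size is 225 × 0.8 / 1.5 = 120 per arm, with power of about 92.7% (no continuity correction).

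**2. Direction of the error.** Split the between-school variance into a part between strata (B) and a part within strata (W). Under stratified allocation the risk difference varies only through W and the child-level variance. A cluster-only standard error estimates B + W plus the child-level variance. It is therefore too large when B > 0 and right when B = 0. It is not too small on this account.

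**3. Size, many small schools.** Assumed, because the article does not give the number of schools: 17,300 / 200 = 86.5, taken as 86 schools with about 5 eligible children each, residual school SD 0.12, a 10-point difference by size, and an urban-rural gap of 15 or 30 points. The base rate is the protocol's 60% and the effect its 20 points. Simulated results (separate runs differ by about a point):

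| Allocation strata | Gap | Power, cluster only | Power, with strata or location | Type I error, cluster only |
|---|---|---|---|---|
| Location and size | 15 | about 96% | about 97% | about 4.1% |
| Location and size | 30 | about 93% | about 97% | about 2.6% |
| Size only | 15 | about 95% | about 97% | 4.4 to 4.9% (both gaps) |
| Size only | 30 | about 90% | about 97% | 4.4 to 4.9% (both gaps) |

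**4. Size, fewer and larger clusters.** Assumed: 12 to 24 schools per arm, 8 to 15 evaluable children per school (180 to 192 per arm), four equal strata, within-stratum design effect about 1.4, and the same 60% against 80%. School-level intervals with and without stratum terms:

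| Spread in wear across strata | Coverage, cluster only | Extra width | Power, cluster only | Power, with strata |
|---|---|---|---|---|
| 0 points | 95 to 96% | none | 93 to 94% | 92 to 94% |
| 10 points | 95 to 96% | 2 to 3% | 91 to 94% | 92 to 95% |
| 20 points | 96.4 to 97.1% | 8 to 15% | 89 to 93% | 94 to 95% |
| 30 points | 98.1 to 98.9% | 18 to 33% | 79 to 91% | 93 to 96% |

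With stratum terms, coverage stays at 94.5 to 95.8%. Under no effect and a 30-point spread, two-sided error is 1.5 to 2.6% without strata and 5.0 to 5.4% with them.

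**5. Are these scenarios compatible with the protocol's design effect of 1.5?** Take 1.5 as covering all between-school variation, and use 0.6 × 0.4 = 0.24 as the total variance.

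- Step 3, 15-point gap: 0.12² + 0.05² + 0.075² = 0.0225; 0.0225 / 0.24 = 0.094; design effect 1 + 4 × 0.094 = 1.38.
- Step 3, 30-point gap: 0.12² + 0.05² + 0.15² = 0.0394; 0.0394 / 0.24 = 0.164; design effect 1 + 4 × 0.164 = 1.66.
- Step 4, equally spaced strata: the variance between strata is 0.0014, 0.0056 and 0.0125 for spreads of 10, 20 and 30 points. Adding (m − 1) × variance / 0.24 to 1.4, for m = 8 and m = 15, gives about 1.44 to 1.48, 1.56 to 1.72 and 1.76 to 2.13.

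So the 15-point gap and the 10-point spread fit within 1.5, and the larger scenarios exceed it.

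**The case against.** Four objections deserve weight.

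- **The first statement may describe sampling.** It stands under Selection of schools, so it could mean stratified selection, with size the only allocation factor. That is possible, but the text does not say so, and one sentence would settle it.
- **Model terms belong in the analysis plan.** The article is condensed, the plan is not shown, the covariate list is open-ended, and nothing excludes stratum terms. This stands in part: silence alone would be no finding. But the article does more than stay silent. It fixes the adjustment as school only and gives covariates down to their functional form. It places them in a separate analysis that depends on observed imbalance, so adding the strata to that list would not change the main interval.
- **The error is conservative.** This stands in full. False positives do not increase.
- **The sizes rest on invented inputs.** This largely stands. The article gives no urban-rural gap and no number of schools, and 200 is a cut-point between strata, not a mean school size. Also, 86 × 5 = 430 children is closer to the 450 recruited than to the 360 left after 20% loss, so the power figures in step 3 are somewhat favourable. The scenarios with the largest losses imply more clustering than the protocol's own 1.5.

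**Conclusion.** The two sections disagree on the allocation factors, and the analysis as written includes neither factor. The consequence is moderate. If the outcome differs between the strata used for allocation, the cluster-only interval is too wide and some precision is lost. If it does not differ, nothing material changes. At the planned 20-point effect, with 86 schools and a gap of 15 to 30 points, power is about 96% to 93% without strata and about 97% with them. With fewer, larger clusters the loss stays within about two points of power for a 10-point spread. It takes power below 90% only in some scenarios whose design effect exceeds 1.5.

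A reader might infer more, in two ways that the documents do not support.

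- **Chance confounding by location under size-only allocation.** If location was not an allocation factor, chance urban-rural imbalance is part of the randomization variance that the cluster-adjusted interval already covers. Type I error stays at about 4.4 to 4.9%, so adjusting for location would improve precision and would not correct an error.
- **A seriously underpowered trial.** With a 15-point effect and a 30-point gap, simulated power is 65 to 70% without strata against 82 to 84% with them. The protocol plans for 20 points, and no 15-point effect appears in it.

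**What to change.** - Make Selection of schools and Randomization agree on the factors actually used in the allocation. If location served only to select schools, say so. State how the web service was applied within strata.
- Include the allocation factors in the primary and secondary risk-difference models regardless of observed imbalance, with cluster-robust 95% confidence intervals.
- If location was not an allocation factor, prespecifying it as a covariate is optional, for precision.

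The cost is wording and one or two model terms. Both factors are school-level facts known before randomization, so no new data are needed, and the sample size does not change. Settle it before the outcome data are analysed by arm.
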